**Methods:**

This study is a randomized controlled trial with 2 arms, using within-therapist randomization (ABAB design) in outpatient psychotherapy. Participants are recruited offline via routine intake procedures. A total of 100 patients will be randomly assigned to one of the two conditions following a waiting period. The inclusion criterion is the existence of any mood disorder (major depressive disorder or anxiety disorder), assessed via a clinical interview. Each therapist treats patients in both conditions. Outcomes will be measured at 4 time points: after diagnosis confirmation, postwaiting period, posttreatment, and a 6-month follow-up. Primary and secondary outcomes, including symptom severity, will be assessed using questionnaires. Data collection also includes patient and therapist session evaluations using the Bern Patient and Therapist Session Questionnaire. In the feedback condition, therapists conduct frequent interviews using time-series data generated from daily self-assessments using the synergetic navigation system, including the Therapy Process Questionnaire and an individualized measure based on case conceptualization.

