## Methods

### Study Design

This study is designed as an RCT with 2 arms, using within-therapist randomization in the real-world clinical practice of routine outpatient psychotherapy in Germany.

Participants are recruited offline through routine intake procedures when presenting for outpatient psychotherapy with participating therapists. Patients who are suspected by the therapist to meet criteria for MDD, AD, or MDD with anxious disorders complex will be briefly screened for their ability and willingness to use a smartphone. If eligible, they will be informed about this study and its requirements by the respective therapist and asked whether they are interested in participating in a research project. Afterward, they will be informed of the procedure and the requirements of this study by the respective therapist. They obtain a flyer with basic information and, in case of concrete interest, will be instructed in detail and obtain an explanation to its full extent.

Patients who have consented to participate in this study will undergo a structured diagnostic interview (Structured Clinical Interview for *DSM-5* [*Diagnostic and Statistical Manual of Mental Disorders* {Fifth Edition}] – Clinician Version) [41] to confirm the inclusion criteria (diagnoses as listed in the Participants section, see below). The interview will be conducted remotely by an independent, trained clinical psychologist who is otherwise not involved in this study. The Structured Clinical Interview for *DSM-5* allows a final decision on including or excluding the patient. In addition to diagnostic confirmation, baseline information on participants’ current medication, concurrent treatment, and symptom severity will be systematically assessed. These variables will be considered as covariates in the main outcome analyses to account for potential prognostic influences. In addition, sensitivity analyses will be conducted to examine whether excluding participants with concurrent treatments or psychopharmacological medication changes affects the robustness of the findings. Following inclusion, a waiting period of 1 (minimum) to 6 months (maximum) begins for each patient, depending on the therapist’s capacity to initiate treatment.

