After the waiting period, a randomization procedure decides on the allocation of a patient to condition A (ASH) or B (ASH+synergetic process management [SPM]). To ensure methodological rigor and internal validity, patients will be randomly assigned to one of the two treatment conditions using therapist-specific block randomization. The predefined block-randomized allocation sequences (eg, ABAB, BABA, AABB, BBAA, ABBA, and BAAB) will be generated in advance by the principal investigator for each therapist to ensure a balanced distribution of conditions within therapists. Patients will be assigned to intervention conditions in the order of study inclusion according to the next position in the respective therapist’s allocation sequence. The allocation sequence will remain concealed from the therapists until each new patient is assigned.

After the randomization, the treatment period starts, whose length depends on the concrete requirements of each patient and must be decided by the patient and therapist together (shared decision-making). In contrast to manualized treatments (adherence to protocol), this is a usual procedure in naturalistic settings. A follow-up assessment will be conducted 6 months after the end of therapy.

There are four assessment points: at the beginning of the waiting period (T1), at the start of the treatment (T2), at the end of the treatment (T3), and at follow-up (T4). The design of this study is illustrated in Figure 1.

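### Blocks of four within each therapist let an unblinded, recruiting therapist deduce up to a third of allocations just before release, and T2 as worded comes after randomisation

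*Protocol article*

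**What the plan says.** Study Design states that "patients will be randomly assigned to one of the two treatment conditions using therapist-specific block randomization". It adds that "predefined block-randomized allocation sequences (eg, ABAB, BABA, AABB, BBAA, ABBA, and BAAB) will be generated in advance by the principal investigator for each therapist", and that "The allocation sequence will remain concealed from the therapists until each new patient is assigned".

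On order and timing, the same section says that "Patients will be assigned to intervention conditions in the order of study inclusion according to the next position" in that therapist's list. It also places the randomisation step after a wait of unequal length: "a waiting period of 1 (minimum) to 6 months (maximum) begins for each patient", governed by the therapist's capacity. Treatment is then described as beginning once randomisation is done. T2 is tied to that beginning: "There are four assessment points: at the beginning of the waiting period (T1), at the start of the treatment (T2").

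The treating therapist suspects the diagnosis, screens for smartphone use and informs the patient: "If eligible, they will be informed about this study and its requirements by the respective therapist". An uninvolved psychologist then confirms the diagnosis. The section on therapist effects says that therapists cannot be blinded, and Bias Minimization names their preferences as a bias concern. The abstract labels the scheme as "using within-therapist randomization (ABAB design) in outpatient psychotherapy"; the aims and Bias Minimization repeat ABAB.

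**The concern.** Concealing a list protects the next assignment only if it cannot be worked out from earlier ones. Here each therapist has a separate list, sees every past assignment in it, and can read in the article that the example blocks have length four. That therapist also decides whom to approach. If a preference for one condition influenced who was brought in or who was lost before randomisation, the comparison of ASH with ASH+SPM, the trial's only randomised contrast, would be biased.

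The second issue is the baseline. T2 carries the self-reported outcomes and the FPTM-23, whose stated purpose is to check for bias between conditions. If the arm is already known when these are answered, the FPTM-23 cannot cleanly separate prior motivation from a reaction to the allocation.

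**Working it through.** **Inputs.** Blocks of two A and two B, separately by therapist (Study Design). 100 patients, 1:1 (Power Considerations). At least 15 therapists (Therapists), so 100/15 = 6.7 patients each if loads are equal. The plan gives no figure for predictability. Its sample size does reproduce: with f = 0.25, two measurements, r = 0.50 and alpha 0.05 (assumed), λ = 0.0625 × 98 × 2/1.5 = 8.17, and power is 0.808 at N = 98.

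**One complete block.** There are C(4,2) = 6 balanced orders, exactly the six listed. An allocation is certain if every order compatible with the known past gives the same arm.

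| Position | Chance it is certain | Best guess correct |
|---|---|---|
| 1 | 0 | 0.500 |
| 2 | 0 | 0.667 |
| 3 | 1/3 (after AA or BB) | 0.667 |
| 4 | 1 | 1.000 |

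Certain share: (0 + 0 + 1/3 + 1)/4 = 33.3%. Best guess: (0.5 + 0.667 + 0.667 + 1)/4 = 70.8%.

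**At this trial's load.**
- 6 patients: 1.333/6 = 22.2%.
- 7 patients: (1.333 + 0.333)/7 = 23.8%.
- 15 therapists, ten with 7 and five with 6: 10 × 1.667 + 5 × 1.333 = 23.3 of 100.
- 20 therapists with 5 each: 20 × 1.333 = 26.7 of 100.
- 25 therapists with 4 each: 33.3 of 100, the maximum.
- Simulated unequal loads over 15 to 25 therapists: about 23 to 28 of 100 on average.

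These figures apply just before release. They hold even if positions fixed at inclusion are revealed in another order, because a balanced random block read in any order that does not depend on its content is still a balanced random block.

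**If selection happens at inclusion.** Earlier patients may still be waiting without an allocation.
- One unallocated: certain share (0 + 0 + 0 + 1/3)/4 = 8.3%; best guess (0.5 + 0.5 + 0.667 + 0.667)/4 = 58.3%.
- Two unallocated: certain share 0%; best guess (0.5 + 0.5 + 0.5 + 0.667)/4 = 54.2%.

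**With varying block sizes.** Sizes 2, 4 and 6 drawn at random with equal chance, enumerated over 7 patients, with the possible sizes known but not the draw: certain share 2.9% against 23.8%, best guess 66.8% against 66.7%. Certainty nearly disappears; guessing does not.

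**T2.** Statistical Analysis compares the T1–T2 period with the T2–T3 period. Suppose that knowing the arm shifts T2 by δ in one arm. The first change (T2 − T1) moves by +δ and the second (T3 − T2) by −δ, so the difference between the two moves by 2δ in that arm. The average of the two changes, (T3 − T1)/2, is unaffected. The documents give no value for δ.

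**The case against.** Several points on the other side are sound.

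- **A third of all allocations is certain.** A reader might infer this, but it is a maximum, reached only if every therapist's load is a multiple of four. That the block length is fixed is also inferred: the sequences are given as examples and no block-size rule is stated. The list is, however, the full set for length four, and no other length appears.
- **Therapists can pick an arm by timing a start.** This is tempting, because the wait depends on the therapist's capacity. Under the written rule positions follow inclusion, so moving a start date does not change a patient's arm. The route opens only if practice follows the order of starts. What remains is whom to approach when few patients are waiting, and loss of an included patient before randomisation.
- **The trial alternates.** ABAB, read literally, is alternation, but Study Design is the operative text and lists six orders. The label is misleading shorthand, not the procedure.
- **No clean baseline exists.** This goes too far. All primary and secondary outcomes are also taken at T1, before allocation. The abstract places the second assessment after the waiting period, which does not settle its order relative to randomisation, and the design figure is not shown. Only the FPTM-23 has no earlier measurement.
- **Small blocks serve a purpose.** They keep the conditions balanced within therapists who treat few patients each.

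None of this removes the deduction available just before release, or the need to state whether T2 precedes allocation.

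**Conclusion.** The concern holds in limited form. Given blocks of four and a therapist who tracks past assignments, about 23 to 28 of 100 allocations can be expected to be certain just before release at realistic loads, with one third as the ceiling. At inclusion the share in a complete block is 8% with one earlier patient unallocated and 0% with two. This measures the opportunity for selection; nothing in the document shows that selection has occurred or that the principal investigator recruits or treats.

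As worded, T2 comes after randomisation, which exposes the T2 outcomes and, more seriously, the FPTM-23 to knowledge of the arm. Study Design also does not explain how positions filled by inclusion fit with randomisation after unequal waits. These points are cheap to correct and should be corrected.

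**What to change.** 1. For sequences not yet used, draw block sizes at random (for example 2, 4 and 6), do not disclose them, and have the list held and released by someone who neither recruits nor treats. This cuts the certain share to about 3%. The best guess stays near 67%, so it is not sufficient alone.
2. Release each allocation only after T2 and the FPTM-23 have been submitted, and state that order in Study Design.
3. Keep the order of inclusion, fix each patient's position when he or she is included, and reword the sentence on randomisation after the wait to match. Do not change to the order of release: that would let the choice of start date decide who takes the next position.
4. Replace the ABAB label in the abstract, aims and Bias Minimization with therapist-stratified block randomisation.

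The cost is slightly looser balance within therapist, regeneration of unused sequences and one check before each release. With 22 of 100 patients enrolled at submission, 78 were still to be enrolled. Sequences already in use should be left as they are, and the date of the change reported.

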### Aims of This Study

This study addresses different research questions. There is some concern regarding the implementation of the procedure into the routine practice of outpatient psychotherapists, which is challenging because of the complexity of the routine process monitoring procedure. It encompasses an assessment of the patient’s personal resources, a case formulation, and, based on this, the development of a personalized process questionnaire. Regular feedback interviews during the sessions are scheduled with reference to the visualized results. Other research questions focus on the outcome of this study’s conditions and on the patterns of change that may characterize successful or unsuccessful therapies. Potential therapists’ implementation effects will be examined based on an ABAB therapist allocation (see the Study Design section). The main research questions are as follows:

Practicability: Can high-frequency process monitoring (daily self-assessments) and feedback interviewing (at least every second session) be implemented in outpatient routine psychotherapy, that is, in naturalistic settings? To what extent is the routine practice of outpatient psychotherapy supported by process monitoring? What can be learned from this study for the implementation of process monitoring into practice and training?Treatment outcomes: What is the efficacy of ASH compared with a waiting period control? What are the differences in the treatment efficacy of the two randomized implementation conditions, ASH versus ASH supported by personalized process monitoring and feedback in self-reported primary and secondary outcomes?Session effects and change dynamics: What are the differences between the implemented conditions in the experienced quality of the sessions (eg, micro-outcome) and in the therapeutic alliance? Does the process feedback support the therapeutic alliance? With reference to the time series created by the daily self-assessments: Are there specific features of the change dynamics (eg, discontinuous pattern transitions and critical instabilities) related to the outcome?Therapist effects: Are there any differences across therapists (therapist effects)? Is there an interaction between potential therapists’ preferences for a particular implementation condition and outcome?

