### Statistical Analysis

The statistical procedure for answering the outcome-related questions of this study is ANOVA with repeated measures, with the groups (conditions) as the between-subject factor and the comparison of the waiting period (T1-T2, level 1) with the overall treatment (T2-T3, level 2) as the within-subject factor. The preference ratings of the therapists in the ASH+SPM condition can be used as covariates in a 1-factor ANOVA with repeated measures.

The therapy effects can be predicted by linear regression models and multilevel regression models with conditions, therapy motivation (patients), alliance rates (patients), and the quality of the implementation as predictors. In the ASH+SPM condition, the preference of implementing the SPM (therapists) and the compliance rates (patients) of the process monitoring can also be used as predictors.

The research questions on the dynamics of change (eg, Are pattern transitions related to the outcome?) will be analyzed by applying the Pattern Transition Detection Algorithm [59] and methods of recurrence quantification analysis [60,61]. The respective quantifiers will be correlated with the outcome measures (T2-T3 and T2-T4).

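### T2 is tied to the start of treatment, so the ASH-versus-waiting contrast covers treatment starters only and can be biased in either direction

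*Protocol article*

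**What the plan says.** The Study Design section names four assessment points, the first three being "at the beginning of the waiting period (T1), at the start of the treatment (T2), at the end of the treatment (T3"). The Abstract lists the same occasions as "after diagnosis confirmation, postwaiting period, posttreatment, and a 6-month follow-up". On the wait itself, Study Design says: "a waiting period of 1 (minimum) to 6 months (maximum) begins for each patient, depending on the therapist’s capacity to initiate treatment". Allocation comes later: "After the waiting period, a randomization procedure decides on the allocation of a patient to condition A (ASH) or B".

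One of the main research questions in Aims of This Study is "What is the efficacy of ASH compared with a waiting period control". Power Considerations and Statistical Analysis both answer it with a repeated-measures ANOVA that takes "the comparison of the waiting period (T1-T2, level 1) with the overall treatment (T2-T3, level 2) as the within-subject factor".

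Three further statements matter. Assessments says that outcomes are completed online in the app and not in sessions. Ethical Considerations says that consent is given before T1. The Abstract counts the 100 patients at random assignment, after the wait. Limitations mentions unequal waiting times but not loss of patients during the wait.

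**The concern.** The waiting period is the only untreated comparison for the ASH efficacy question, and the article states that no controlled efficacy study of ASH exists so far. A patient who recovers, gives up or finds care elsewhere during a wait of up to 6 months never reaches the event that defines T2. That patient's change while waiting is not recorded. The ANOVA needs T1, T2 and T3 from the same person, so it then describes waiting only among people who went on to treatment.

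Randomisation cannot protect this contrast, because it takes place after the selection. If leaving is related to how patients changed while waiting, the comparison of waiting with treatment is distorted. Without an end-of-wait score from the leavers, nobody can tell in which direction or by how much.

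**Working it through.** **1. The plan's own figures.** Inputs from Power Considerations: f=0.34 (from d=0.68), r=0.50, two measurement points, N=32; and f=0.25, N=98 for the between-group comparison. Alpha is not stated; 0.05 is assumed.

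- Within: λ = N·m·f²/(1−r) = 32·2·0.1156/0.5 = 14.80, with 1 and 30 df. Power is 0.961 (stated 96%), and 32 is the smallest N that reaches 0.95 with two groups.
- Between: λ = N·m·f²/(1+(m−1)r) = 98·2·0.0625/1.5 = 8.17, with 1 and 96 df. Power is 0.808 (stated 80%), and 98 is the smallest N.

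Both reproduce. The 100 are counted after the wait, so loss during the wait does not reduce them. It only raises the number to include at T1: 100/0.9, 100/0.8 and 100/0.7 give 112, 125 and 143 for 10, 20 and 30% attrition.

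**2. Why dropping leavers from both periods does not cancel the selection.** Take outcome SD 1 at each time and r=0.50 between every pair. Let W = T1−T2 (improvement while waiting) and X = T2−T3 (improvement under treatment).

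- Var(W) = Var(X) = 1+1−2·0.5 = 1.
- Cov(W,X) = 0.5−0.5−1+0.5 = −0.5.

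Both changes contain T2, so they correlate at −0.5. If selection lowers mean W among starters by δ, it raises mean X by 0.5δ. The contrast X−W then moves by 1.5δ.

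**3. Size of the shift.** Assume that a fraction p leaves and that the tendency to leave correlates 0.5 with W. Then δ = 0.5·φ(z)/(1−p), where z is the (1−p) quantile of the standard normal.

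| p | φ(z)/(1−p) | δ | 1.5δ |
|---|---|---|---|
| 10% | 0.195 | 0.098 | 0.146 |
| 20% | 0.350 | 0.175 | 0.262 |
| 30% | 0.497 | 0.248 | 0.373 |

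**4. Simulation check** (2,000,000 patients; assumed mean waiting improvement 0.10 and treatment improvement 0.68, so the full-cohort contrast is 0.58):

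| Who leaves | 10% | 20% | 30% |
|---|---|---|---|
| Improvers | 0.73 | 0.84 | 0.95 |
| Patients who worsen | 0.43 | 0.32 | 0.21 |
| At random | 0.58 | 0.58 | 0.58 |
| Low T1 severity | 0.53 | 0.49 | 0.46 |
| High T1 severity | 0.63 | 0.67 | 0.70 |

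The simulated shifts agree with step 3. Against the planning effect, 0.15/0.68 = 0.22 and 0.37/0.68 = 0.54.

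**The case against.** **The two labels for T2 may be one time point.** Study Design runs the end of the wait, randomisation and the start of treatment together, and the analysis sections call T1-T2 the waiting period. This stands: a reader might infer that Abstract and Methods contradict each other, but they name the same juncture. For patients who never start, however, only the treatment-based definition is given, and no end-of-wait measurement is scheduled for them.

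**The direction is unknown.** A reader might infer that the design inflates the ASH effect, since recovery removes the reason to start therapy. The documents do not support that as a fact. They give no reasons for leaving, and patients who worsen may equally seek care elsewhere, which would understate the effect.

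**Missing-data handling belongs in an analysis plan that is not shown.** This is true of the choice of model. It does not cover the timing of T2, which the article fixes itself. An end-of-wait score that was never collected cannot be restored at analysis.

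**The effect among starters is a legitimate target.** It is, and it should be kept under its own name. But the research question is put without that restriction. Selection that involves T2 also distorts the before-after contrast among starters through the shared score.

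**The scope is narrow.** This stands. Losses precede randomisation, so ASH versus ASH+SPM keeps its internal validity.

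**Conclusion.** The point holds as a limited one. As scheduled, the ASH-versus-waiting contrast is conditional on starting treatment and open to bias of unknown sign. With 10-30% attrition and a correlation of 0.5 between leaving and change during the wait, the shift is about +0.15 to +0.37 SD if improvers leave, the same amount downward if patients who worsen leave, and zero if leaving is random. That is roughly a fifth to a half of the planning d of 0.68. The attrition rates, the correlation, the equal variances and the use of r=0.50 between every pair of time points are assumptions; only r=0.50 and d=0.68 come from the article.

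A reader might go further and infer that a given share of the planned effect is artefact, that the sample size is too small, or that the randomised comparison is compromised. None of these follows: the sign is open, both sample sizes reproduce and are counted after the wait, and the selection occurs before allocation.

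**What to change.** Define T2 as the end of the waiting period for every included patient. Send the existing online outcome questionnaires when a treatment slot becomes available, or when the patient says that they will not start, and at the latest at 6 months, whether or not treatment begins.

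Estimate the waiting-period change from all patients with a T1, using a mixed model. Keep the starters-only contrast as a second, named estimand. Report how many left during the wait, their T1 scores and their reasons.

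The cost is one changed sentence in the schedule and one extra online questionnaire for non-starters, some of whom will not answer. The model also has to assume that the T3 of non-starters is missing at random, although they never received the treatment; this is why both estimands should be shown. The change is still timely: Results reports 22 participants enrolled and no outcome analyses so far.
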